**Methods:**

This study is a multicentre, double-dummy, single-blind, randomized, active-controlled trial. Two hundred and one eligible participants will be randomly assigned into three groups: a verum acupuncture plus placebo group, an itopride plus sham acupuncture group, and a sham acupuncture plus placebo group. This study consists of a 1-week screening period, a 4-week treatment period, and a 12-week follow-up period. During the intervention period, participants will receive 12 sessions of verum or sham acupuncture treatment (one session per day, three sessions per week, for 4 weeks) along with 50 mg itopride tablets or 50 mg itopride placebo tablets 3 times a day for 20 days (5 continual days a week for 4 weeks). The response rate (patients who had adequate relief of gastric symptoms will be considered positive responders) and the elimination rate of cardinal symptoms (postprandial fullness and early satiation) are the primary indicators to evaluate the overall acupuncture effect for PDS. Secondary outcome measures will include the Nepean Dyspepsia Symptom Index (NDSI), the short form-Nepean Dyspepsia Life Quality Index (SF-NDLQI), the Hospital Anxiety and Depression Scale (HADS), and related hormone concentrations. Participants’ expectations toward acupuncture treatment will also be assessed, and adverse events will be recorded for safety assessment. All analyses will adhere to an intention-to-treat principle.

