### Sample size calculation

2.11

The sample size for this study was determined based on the responder proportion at the end of a 4-week treatment, with 70.69% for the acupuncture treatment and 55.46% for the itopride treatment, as reported in a previous study (30). The sample size calculation was performed using PASS 15.0 software, with a 1:1 ratio between the verum acupuncture plus placebo group and itopride plus sham acupuncture group. A statistical power of 80% (*β* = 0.2), a one-sided alpha of 0.025 (*α* = 0.025), and a non-inferiority margin of −10% (*Δ* = −10%) were considered in the calculation. The resulting sample size was 57 for each group. Accounting for a 15% dropout rate, each group needed 67 cases, resulting in a total enrollment of 201 cases across three groups.

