### Statistical analysis

2.12

Efficacy analyses will be performed on all patients who were randomized, adhering to the intention-to-treat principle. This approach ensures that all patients are included in the analysis based on the group to which they were initially assigned, regardless of whether they completed the study as intended. Missing data on the primary outcome will be imputed using the multiple imputation method under the missing at-random assumption. If there are significant differences in baseline variables between the two groups, those unbalanced variables will be included as covariates in the analysis of the primary outcome.

We will establish confidence intervals at a 95% level, with a significance level set at 0.05. Continuous data will be reported as mean ± standard deviation (SD) if it is normally distributed. Otherwise, it will be reported as median (interquartile range). For longitudinal continuous data, we will compare groups using repeated-measures analysis of variance (ANOVA), taking into account both group and time-group interactions. Student’s t-test or Wilcoxon rank-sum test will be used for other continuous data. For categorical data, Χ^2^ test or Fisher’s exact test will be applied as appropriate. The strength of linear relationships between variables will be evaluated using linear correlation analysis, and sensitivity analysis will be performed if required. The occurrence of AEs between groups will be summarized using descriptive analysis.

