To our knowledge, this is the first multicenter, randomized, double-dummy, single-blind, active-controlled trial assessing the efficacy and safety of acupuncture for treating PDS. In this trial, we will implement blinding among participants to reduce the potential influence of patient preference for acupuncture on the study results. Furthermore, we plan to adopt stringent quality control measures, blinded outcome assessments, ensured concealed treatment allocation, and intention-to-treat analysis to minimize bias and enhance the credibility of our findings. However, several limitations of this trial should be noted. Although participants and assessors are blinded in this trial, treatment personnel can not be further blinded due to the inherent nature of acupuncture. Therefore, it cannot be ruled out that performance bias influences the results. Second, this trial only includes patients from Changsha City; whether the results can be applied to other populations or regions requires further research. Finally, the proposed acupuncture regimen is standardized dose not account for individual differences among patients, which may limit the efficacy of the acupuncture treatment.

To summarize, the outcome of this study aims to validate the difference of effectiveness and safety between acupuncture and Itopride in treating PDS. These results will serve as a dependable foundation to endorse the practical use of acupuncture in managing FD.

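### The sample size is for non-inferiority (margin −10 points), but the analysis section names only zero-difference tests for binary outcomes and never uses the margin, so the stated 80% power does not belong to the named test

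*Protocol article*

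**What the plan says.** Section 2.11 (Sample size calculation) bases the size on the responder proportion at the end of the 4-week treatment, "with 70.69% for the acupuncture treatment and 55.46% for the itopride treatment". It uses "a one-sided alpha of 0.025", 80% power and "a non-inferiority margin of −10" percent, for the verum acupuncture plus placebo arm against the itopride plus sham arm at 1:1. The result is 57 per group, raised to 67 for 15% dropout, or 201 over three arms.

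Section 2.12 (Statistical analysis) sets the inferential standard: "We will establish confidence intervals at a 95% level, with a significance level set at 0.05". It assigns methods by data type, and categorical data go to a chi-square or Fisher's exact test. For the primary outcome it adds multiple imputation and adjustment for unbalanced baseline variables. It gives no margin, no non-inferiority hypothesis and no rule for reading the interval.

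Both primary outcomes in section 2.7.1 (proportion of responders and elimination rate) are proportions. The term non-inferiority occurs in section 2.11 only. Section 2.1 says the trial compares acupuncture with itopride. The Discussion closes by saying that "the outcome of this study aims to validate the difference of effectiveness and safety between acupuncture and Itopride in treating PDS".

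**The concern.** A chi-square or Fisher's exact test addresses the hypothesis that two proportions are equal. The margin does not enter it. A non-significant result does not show non-inferiority, and a result that does establish non-inferiority can be non-significant on such a test. The plan is therefore powered for one question, while the only tests it names for a binary outcome, and the closing statement of aim, address another.

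Two things are at stake. A reader will attach the stated 80% to the named test, which has about half of that. And the confirmatory claim is left open on the main comparison, so whether the trial is judged on non-inferiority or on a difference could be settled after the results are known.

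**Working it through.** **Inputs (section 2.11).** Responder rates pA = 0.7069 and pI = 0.5546, so the difference is 0.1523. Margin 0.10, one-sided alpha 0.025 (z = 1.960), power 80% (z = 0.842), 57 evaluable and 67 enrolled per group. From section 2.12: level 0.05, taken as two-sided because its sidedness is not stated.

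**1. Reproducing the plan's figure.**
- Sum of variances: V1 = 0.7069×0.2931 + 0.5546×0.4454 = 0.4542.
- Distance from the margin: 0.1523 + 0.10 = 0.2523.
- n = (1.960 + 0.842)² × 0.4542 / 0.2523² = 56.01, rounded up to 57. This agrees with the plan.
- Dropout: 57/0.85 = 67.06. The plan states 67; strict rounding up gives 68, which is immaterial.

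**2. Power of the named test at the same rates.**
- Mean rate (0.7069 + 0.5546)/2 = 0.63075; null variance V0 = 2×0.63075×0.36925 = 0.4658.
- Power = Φ[(0.1523 − 1.960×√(V0/n)) / √(V1/n)].
- n = 57: (0.1523 − 1.960×0.0904)/0.0893 = −0.279, power 39.0%.
- n = 67: (0.1523 − 1.960×0.0834)/0.0823 = −0.135, power 44.6%.
- Exact enumeration: chi-square 39.4% and 44.8%; Fisher 31.5% and 38.2%.
- Size for 80%: (1.960×√0.4658 + 0.842×√0.4542)² / 0.1523² = 156.4, so 157 evaluable, or 157/0.85 = 184.7, so 185 enrolled per group.

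**3. Power if the lower 95% limit is compared with −10 points.**
- Power = Φ[0.2523/√(V1/n) − 1.960].
- n = 57: 0.2523/0.0893 − 1.960 = 0.866, power 80.7%.
- n = 67: 0.2523/0.0823 − 1.960 = 1.104, power 86.5%.
- Exact enumeration of the Farrington-Manning score test at 57 gives 80.0%.

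| Per group | Non-inferiority by the interval | Chi-square for a difference |
|---|---|---|
| 57 | 80.7% | 39.0% |
| 67 | 86.5% | 44.6% |

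**4. The expected result, read both ways.** With 67 per group the planning rates give about 47 and 37 responders (67×0.7069 = 47.4; 67×0.5546 = 37.2).
- Difference 10/67 = 0.149.
- Chi-square without continuity correction: p = 0.074, not significant.
- Wald 95% interval: 0.149 ± 1.960×0.0826, that is −1.3 to +31.1 points. The lower limit is well above −10.

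The same data fail the named test and meet the powered criterion.

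**The case against.** The strongest reply is that the plan already holds the parts of a non-inferiority analysis. Section 2.11 fixes the margin, direction, alpha and pair of arms, and section 2.12 plans 95% intervals. If those are two-sided, the lower limit is a one-sided 0.025 test. This stands. A reader might infer that the plan allows only a difference test, or that 0.05 conflicts with 0.025; neither follows. What does not follow either is that the plan makes the link: nothing in it compares the interval with −10 points.

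The categorical-data sentence is also generic. It does not name the primary outcome, and a plain chi-square test could not carry the covariates that 2.12 allows for. That is fair, but 2.12 names no other test for a proportion.

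A separate analysis plan may hold the decision rule. It may, and absence of detail is not the point here. The article itself names a level, tests and an aim, and these do not fit its own sample size. The Discussion sentence is loosely worded and section 2.1 is compatible with non-inferiority, so they are weak evidence of a contrary hypothesis. They still do not state the powered one.

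Three stronger readings go too far:
- **That the sample size is wrong.** It reproduces, and it suits the non-inferiority reading.
- **That the authors will misread a null result.** The documents give no basis for predicting this.
- **That the analysis is invalid because "All analyses will adhere to an intention-to-treat principle".** Intention-to-treat alone can be non-conservative for non-inferiority, but no bias has been shown here, and supporting analysis sets are commonly left to an analysis plan.

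**Conclusion.** The point holds as a mismatch between sections 2.11 and 2.12. The stated 80% belongs to a non-inferiority test that the analysis section does not describe. The test it does name for binary data has about 39% power at 57 per group and 45% at 67, and would need about 157 evaluable per group for 80%. This is more than missing detail, because the named test cannot deliver the conclusion that was powered.

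The figures rest on the planning rates in 2.11 and on 0.05 being two-sided. Using a one-sided 0.05 level instead (z = 1.645 in step 2) gives Φ(0.040) = 52% and Φ(0.184) = 57%, still well short of 80%. The low power matters only if a difference is the primary claim. If non-inferiority is meant, the sample size stands at the planning rates.

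**What to change.** In section 2.12, state that the primary comparison is non-inferiority of verum acupuncture plus placebo to itopride plus sham acupuncture on the proportion of responders at the end of the 4-week treatment. Non-inferiority is concluded if the lower limit of the two-sided 95% confidence interval for the risk difference (acupuncture minus itopride) exceeds −10 percentage points. Compute the interval consistently with the planned multiple imputation.

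Test superiority on the same endpoint and the same pair of arms only after non-inferiority is shown. This order needs no alpha adjustment within that endpoint and comparison; it does not cover the elimination rate or the comparisons with the sham-plus-placebo arm. Align the objective in 2.1 and the closing sentence of the Discussion.

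If a difference is in fact the intended primary claim, say so and restate the power as about 39–45%, or re-size to about 185 enrolled per group.

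A per-protocol analysis may be added as supportive but is not needed to resolve this point. The choice of interval method can stay with the analysis plan.

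The first route costs wording only, with no added patients, visits or data. As the trial is reported to be in progress, make the change before any outcome is examined by arm.

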### Outcome

2.7

Primary outcomes in this study include the proportion of responders (PR) and the elimination rate of the main symptom. The secondary outcomes include changes in symptom score, QOL, mood during the treatment and follow-up, and the participants’ expectancy for acupuncture before treatment, as well as related hormone concentrations. Table 2 display a summary of all measurements. Follow-up for all participants can be completed via social media (WeChat) or phone.

**Table 2 tab2:** SPIRIT figure for the schedule of enrollment, interventions, and assessments.

	Study period								
	Enrolment	Allocation	Treatment phase				Follow-up		
Timepoint**	*1w*		*2w*	*3w*	*4w*	*5w*	*9w*	*13w*	*17w*
Enrolment									
Eligibility screen	X								
Informed consent	X								
Allocation		X							
Interventions									
Verum acupuncture plus placebo									
Itopride plus sham acupuncture									
Sham acupuncture plus placebo									
Assessments									
Proportion of responders			X	X	X	X	X	X	X
Elimination rate			X	X	X	X	X	X	X
NDSI		X				X	X	X	X
SF-NDLQI		X				X	X	X	X
HADS		X				X	X	X	X
Acupuncture expectation		X							
Related hormone concentrations		X				X			
Adverse events			X	X	X	X			

SPIRIT, standard protocol items: recommendations for interventional trials; NDSI, the nepean dyspepsia symptom index; SF-NDLQI, the short form - Nepean Dyspepsia Life Quality Index; HADS, Hospital Anxiety and Depression Scale.

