#### Primary outcome

2.7.1

**The proportion of responders (PR)** Patients experiencing sufficient alleviation of stomach discomfort are categorized as positive responders (23). Participants will be requested to evaluate changes in their symptom relief over the preceding 7 days via a 7-point Likert scale. This scale features options such as “extremely worsened,” “worsened,” “slightly worsened,” “no change,” “slightly improved,” “improved,” or “extremely improved,” which correspond to scores ranging from 0 to 6. Those participants who report a relief score of either 5 or 6 points will be deemed positive responders. The measurement of PR will take place at weeks 2, 3, 4, 5, 9, 13, and 17.

**The elimination rate (ER)** ER refers to the proportion of patients whose main symptoms have disappeared. According to Rome IV criteria, we define postprandial fullness and bloating as the main symptoms. Included patients should have at least one of these symptoms. Using a 7-point Likert scale, the main symptoms are considered to have disappeared if the rating drops to 0 after treatment. ER will be measured at weeks 2, 3, 4, 5, 9, 13, and 17.

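### The only tests Section 2.12 names for the two binary primary outcomes, chi-square and Fisher, cannot use their seven visits, the institution strata or the covariates the section promises

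*Protocol article*

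**What the plan says.** Section 2.12 of the protocol article assigns methods by type of data. For continuous outcomes followed over time it states "For longitudinal continuous data, we will compare groups using repeated-measures analysis of variance (ANOVA", with group and time-by-group terms. For categorical data, the chi-square "test or Fisher’s exact test will be applied as appropriate". No longitudinal method is named for categorical data.

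Section 2.7 makes two binary outcomes primary: "Primary outcomes in this study include the proportion of responders (PR) and the elimination rate of the main symptom". Section 2.7.1 gives both the same schedule: "The measurement of PR will take place at weeks 2, 3, 4, 5, 9, 13, and 17", and "ER will be measured at weeks 2, 3, 4, 5, 9, 13, and 17". Weeks 2 to 5 fall in treatment, and weeks 9, 13 and 17 in the 12-week follow-up.

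Section 2.12 makes two further statements about the primary outcome. If baseline variables differ significantly, "those unbalanced variables will be included as covariates in the analysis of the primary outcome". For incomplete data, "Missing data on the primary outcome will be imputed using the multiple imputation method under the missing at-random assumption". Section 2.4 stratifies randomisation by clinical institution. Section 2.11 sizes the trial on PR at the end of the 4-week treatment.

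**The concern.** The secondary scales (NDSI, SF-NDLQI, HADS), with five assessments each, receive a method that uses all visits together. The two primary outcomes, with seven assessments each, fall under tests for a single cross-tabulation. Taken as written, those tests:

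- cannot link a patient's visits or estimate how the arm difference changes over time;
- take no account of the institution strata;
- cannot carry the covariates promised two sentences earlier for the same outcomes;
- sit awkwardly with multiple imputation, since a Fisher p-value brings no estimate and standard error to pool.

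At stake are a primary analysis whose stated parts do not fit together, and follow-up data on the primary outcomes with no stated way of being used jointly.

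**Working it through.** **1. The protocol's own figure.** Inputs from Section 2.11: PR 70.69% (acupuncture) and 55.46% (itopride), margin −10 points, one-sided alpha 0.025, power 80%.

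- Variance sum: 0.7069 × 0.2931 + 0.5546 × 0.4454 = 0.4542.
- Distance from the margin: 0.1523 + 0.10 = 0.2523.
- n = 0.4542 × (1.960 + 0.842)² / 0.2523² = 56.006, rounded up to 57 per group, as stated.
- With 15% dropout: 57 / 0.85 = 67.06, against the stated 67.

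The sample size is not in question here.

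**2. Precision at one visit.** With 67 per arm, SE = √(0.4542 / 67) = 0.0823 and the 95% CI half-width is 1.96 × 0.0823 = 16.1 points.

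**3. Precision of a mean over weeks 9, 13 and 17.** Assume the rates above hold through follow-up, data are complete, and any two visits of a patient have correlation ρ. The protocol gives neither ρ nor follow-up rates. The variance is multiplied by (1 + 2ρ)/3.

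| ρ (assumed) | Variance factor | SE | 95% half-width | SE reduction |
|---|---|---|---|---|
| 0.3 | 0.533 | 0.0601 | 11.8 points | 27% |
| 0.5 | 0.667 | 0.0672 | 13.2 points | 18% |
| 0.7 | 0.800 | 0.0736 | 14.4 points | 11% |
| 0.9 | 0.933 | 0.0795 | 15.6 points | 3% |

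No matching figure can be given for ER, because the protocol states no ER rates.

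**4. Precision at one visit from a longitudinal model.** In a simulation (400 trials, 67 per arm, three visits, complete data), a GEE with arm-by-visit terms gave a week-17 difference identical, to rounding, to the raw difference in proportions. The same reasoning applies to week 5: with arm-by-visit unconstrained, the sized contrast neither gains nor loses.

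**5. If the effect fades.** As an illustration, let the difference fall linearly: 15.2 points at week 9, 7.6 at week 13, 0 at week 17. The mean is 7.6 points. With ρ = 0.5 and the same SE of 0.0672, two-sided power at 0.05 is Φ(0.0762/0.0672 − 1.96) = Φ(−0.83), about 20%. Week 9 alone has about 45%. With a persistent 15.2-point effect the mean would have Φ(0.1523/0.0672 − 1.96) = Φ(0.31), about 62%.

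**The case against.** The strongest reply is that the gain in step 3 comes from changing the question. It compares a single-visit effect with a three-visit mean that the protocol never defines. This stands: for the sized comparison, or any one visit with complete data, the longitudinal model offers essentially no extra precision, and under fading the mean can be the poorer choice.

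Three stronger readings are tempting, and the documents do not support them.

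- A reader might infer that the plan is to run a separate test at each visit. Section 2.12 does not say so. The covariate sentence implies some regression model for the primary outcome, although none is named.
- A reader might infer that a question about durability over 12 weeks is being answered imprecisely. The stated aim is efficacy and safety against itopride, and the sample size rests on the end of treatment. Follow-up visits are scheduled, but durability is not an objective.
- A reader might infer that the primary comparison is weakened or biased. Nothing here shows that.

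Two further replies have partial force. Multiple imputation could recover much of the between-visit information when data are missing, if its model includes the other visits, which the article does not specify. Working correlation and similar details do belong in an analysis plan, which is not shown. But Section 2.12 is not silent: it names a longitudinal method, limits it to continuous data, and names a different method for categorical data. An analysis plan that followed this text would inherit the mismatch.

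**Conclusion.** The point holds as one of coherence and efficiency. The only tests named for PR and ER cannot accommodate the repeated visits, the institution strata or the covariates that Section 2.12 itself calls for.

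The precision at issue is confined to a follow-up average. The PR half-width would be 11.8 to 15.6 points instead of 16.1, an SE reduction of 27% down to 3%. That range rests on 67 per arm, complete data, persistence of the end-of-treatment rates and an assumed correlation of 0.3 to 0.9. The gain is essentially nil at any single visit with complete data, and an averaged contrast loses power if the effect wanes. The end-of-treatment comparison is not shown to be biased.

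**What to change.** In Section 2.12, replace chi-square/Fisher for PR and ER with one repeated-measures binary model for each outcome, for example a GEE with robust standard errors clustered on patient, fitted to the multiply imputed data. Include arm, visit, arm-by-visit, institution and any planned baseline covariates.

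Report marginal risk differences with 95% CIs:

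- week 5 as the main contrast, since it is the end of treatment and the basis of the sample size;
- weeks 9, 13 and 17 individually, from the same model;
- optionally, the mean of those three weeks, labelled as a supportive follow-up summary and read beside the visit-specific estimates so that fading stays visible.

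Keep chi-square or Fisher for categorical variables measured once. The cost is a change of wording and modest programming, with no new data, visits or patients. It should be fixed before unblinding, so that the choice among follow-up visits is not made after seeing results.

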#### Secondary outcome

2.7.2

**The Chinese version of the Nepean Dyspepsia Symptom Index (NDSI)** The NDSI is a validated dyspepsia-specific questionnaire that quantifies the severity of 15 upper gastrointestinal symptoms in patients with FD over the past 14 days (24). Each symptom is assessed along three dimensions: frequency, intensity, and degree of interference with daily activities. The higher the NDSI total score, the more severe the dyspeptic symptoms are. During the study, NDSI scores were measured at weeks 1, 5, 9, 13, and 17.

**The Chinese version of Short Form-Nepean Dyspepsia Life Quality Index (SF-NDLQI)** The SF-NDLQI instrument is an FD-specific 10-item questionnaire that assesses the impact of upper gastrointestinal symptoms on QOL across 5 domains: tension, interference with daily activities, eating/drinking, knowledge/control, and work/study (25). Each domain has two items, and each item is scored from 1 to 5, with lower scores better quality of life. In this study, the SF-NDLQI will be administered at weeks 1, 5, 9, 13, and 17.

**The Chinese version of the Hospital Anxiety and Depression Scale (HADS)** The HADS will be employed to evaluate the anxiety and depressive symptoms of patients. This scale consists of 7 items for anxiety (HADS-A) and 7 items for depression (HADS-D), with each item scored from 0 to 3, resulting in a total subscale score range of 0 to 21 (26). Higher scores reflect greater levels of anxiety or depression (27). The HADS has demonstrated strong reliability and validity in screening for anxiety and depression among general medical patients (28). Assessments utilizing the HADS will be conducted at weeks 1, 5, 9, 13, and 17.

**Acupuncture expectation** The Expectation for Treatment Scale (ETS), developed by Jürgen Barth and his colleagues, will be utilized to evaluate patients’ acupuncture expectations before treatment (29). This scale comprises 5 items, such as “I anticipate that the treatment (acupuncture) will alleviate my complaints.” Each item is rated on a scale from 1 to 4, representing partial disagreement, partial agreement, agreement, and definite agreement, respectively. The total score ranges from 5 to 20. A higher total scale score indicates a greater expectation of achieving positive clinical outcomes. The ETS will be measured at week 1.

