**Laboratory tests** Serum levels of motilin, gastrin, and ghrelin will be measured using enzyme-linked immunosorbent assays. Fasting venous blood samples (2 mL) will be collected at baseline and after 4 weeks of treatment from all study participants and stored at −80°C until analysis. Laboratory tests will be performed by trained laboratory professionals blinded to treatment assignment.

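### Repeated-measures ANOVA for NDSI, SF-NDLQI and HADS, with imputation and covariates planned for the primary outcome only, does not deliver the promised all-randomised analysis and does not adjust for baseline

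*Protocol article*

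**What the plan says.** All references are to the protocol article.

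- **Analysis set** (Statistical analysis, 2.12): "Efficacy analyses will be performed on all patients who were randomized, adhering to the intention-to-treat principle". The next sentence adds: "This approach ensures that all patients are included in the analysis based on the group to which they were initially assigned", whether or not they completed the study.
- **Missing data** (2.12): "Missing data on the primary outcome will be imputed using the multiple imputation method under the missing at-random assumption". No rule is given for any other outcome.
- **Covariates** (2.12): where baseline variables differ significantly, "those unbalanced variables will be included as covariates in the analysis of the primary outcome". No covariate is planned for secondary outcomes.
- **Method for longitudinal continuous data** (2.12): "we will compare groups using repeated-measures analysis of variance (ANOVA), taking into account both group and time-group interactions". Other continuous data get a t-test or rank-sum test.
- **Visits** (Secondary outcome, 2.7.2, and Table 2): "NDSI scores were measured at weeks 1, 5, 9, 13, and 17"; SF-NDLQI and HADS follow the same schedule. Blood for motilin, gastrin and ghrelin "will be collected at baseline and after 4 weeks of treatment from all study participants".
- **Dropout**: the Sample size calculation (2.11) assumes 15% and enrols 67 per arm. The dropout criteria (2.3.3) include symptoms that fail to improve and worsen after treatment.

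**The concern.** Three choices made in one section do not fit together. The analysis set is everyone randomised. The named method, in its classical least-squares form, needs a complete row of visits for each patient. The one device that could fill the gaps, multiple imputation, is confined to the primary outcome. Followed literally, the plan analyses completers for the three patient-reported scales while describing the result as intention-to-treat.

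The second issue is baseline. Each scale is measured before treatment, but no secondary analysis uses that value as a covariate. If week 1 enters as a level of the time factor, the group main effect averages in a visit at which no treatment effect can exist. If it does not enter, the baseline measurement goes unused.

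At stake are the size and composition of the analysed sample and the precision of the symptom, quality-of-life and mood comparisons. The two primary outcomes are not touched.

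**Working it through.** **1. The plan's own figures.** Inputs from section 2.11: responder proportions 0.7069 and 0.5546, margin 0.10, one-sided alpha 0.025, power 80%.

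n = [0.7069(0.2931) + 0.5546(0.4454)] × (1.960 + 0.842)² / (0.1523 + 0.10)² = 56.006, rounded up to 57. This reproduces the stated 57. Dividing by 0.85 gives 67.06, against the stated 67; strict rounding up would give 68, which is immaterial here.

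**2. Patients left after complete-case selection.**
- At 15% dropout: 67 × 0.85 = 56.95, about 57 per arm. Over three arms 201 × 0.85 = 170.85, about 171, so about 30 randomised patients are left out.
- If visits are instead missed independently at rate q (assumed; the protocol gives no rate), all four post-baseline visits are present in 201 × (1 − q)⁴ patients: about 185 at 2%, 164 at 5% and 132 at 10%.

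**3. Precision and power.** Assumptions, none of them from the protocol: unit variance at each visit, compound symmetry with correlation r, a constant effect d = 0.45 SD at weeks 5 to 17, a two-arm comparison, and n = 57 per arm for every analysis so that sample size does not drive the result. Power = Φ(signal / √(2V/n) − 1.96).

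| Analysis | Signal | V | V at r = 0.5 | Power at r = 0.5 |
|---|---|---|---|---|
| ANOVA group effect, weeks 1–17 | 0.8d = 0.36 | (1 + 4r)/5 | 0.600 | 0.36/0.1451 = 2.48; 70% |
| ANOVA group effect, weeks 5–17 | d = 0.45 | (1 + 3r)/4 | 0.625 | 0.45/0.1481 = 3.04; 86% |
| Baseline-adjusted average, weeks 5–17 | d = 0.45 | (1 + 3r)/4 − r² | 0.375 | 0.45/0.1147 = 3.92; 97.5% |

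The factor 0.8 is the dilution by one fifth: four visits out of five carry the effect.

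Range over the assumed correlation, same d and n:

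| r | Weeks 1–17 | Weeks 5–17 | Baseline-adjusted |
|---|---|---|---|
| 0.3 | 83% | 94% | 97% |
| 0.5 | 70% | 86% | 97.5% |
| 0.7 | 60% | 78% | 99% |

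**4. Does the time-by-group term make up the loss?** It uses week 1 as change from baseline.
- As a single-degree-of-freedom contrast, V = (1 + 3r)/4 + 1 − 2r = 0.625 at r = 0.5, so power is again 86%.
- As the four-degree-of-freedom interaction test, the noncentrality is (57/2) × 0.45² × 0.8 / 0.5 = 9.23, which gives about 67%.

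Neither reaches the adjusted analysis.

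**5. Bias.** One illustrative simulation used r = 0.5, an effect of 0.4 SD in favour of treatment, dropout driven by the week 5 score, and 83% retained. The completer estimate was −0.389, against −0.398 with full data. Bias was small in that scenario; other dropout patterns could give more.

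**6. A single post-treatment value, as for the hormones.** Adjusting for baseline multiplies the variance by 1 − r²: 0.91, 0.75 and 0.51 at r = 0.3, 0.5 and 0.7.

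**The case against.** The strongest reply is that the article never says incomplete patients are deleted, that a least-squares fit is used, or that week 1 is a level of the time factor. These are properties of one implementation, and an analysis plan that is not shown may settle them. That is correct, so a reader who infers that the plan drops every patient with a missed visit, or treats baseline as an outcome, goes further than the text. What remains is that the article itself chose the method and wrote imputation and covariates for the primary outcome only. A later document can repair this only by adding to or departing from section 2.12.

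Other stronger readings also fail:
- **Baseline is wasted.** If week 1 is a repeated level, the time-by-group term uses it as change, which fits the outcome definition in section 2.7. It is then used inefficiently, not discarded.
- **Completer analysis biases the result.** The listed dropout reasons make this possible; nothing in the documents shows it, and the simulation found little.
- **Power falls from 99% to 70%.** That sets 67 fully observed patients per arm (98.9%) against 57 with week 1 included. At 57 in both, with weeks 5 to 17 only, it is 97.5% against 86%. A mixed model does not recreate unobserved visits.
- **No contrast is fixed.** Time points and pairwise comparisons for secondary outcomes are commonly left to the analysis plan, so their absence is not a fault here.
- **The visits are unevenly spaced.** They are four weeks apart throughout.
- **Hormones will get unadjusted two-sample tests.** With two measurements they might count as longitudinal. Under either reading no baseline covariate is stated.

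**Conclusion.** The point holds in limited form. As written, section 2.12 does not deliver its all-randomised promise for NDSI, SF-NDLQI and HADS, and leaves their baseline scores out as covariates. At the protocol's 15% dropout, a classical fit would analyse about 171 of 201 patients.

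The loss of patients rests on the classical form of the method. The power figures rest on assumed correlation, effect size and compound symmetry. Most of the power gain comes from baseline adjustment and avoiding dilution, not from the extra patients: for the adjusted average, 57 against 67 per arm changes power by only about 1.4 points. The change is worth making because it improves a stated method at almost no cost. The primary non-inferiority result is not in question.

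**What to change.** In section 2.12, or in the analysis plan with a matching correction to the article's text:

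1. Replace the ANOVA for NDSI, SF-NDLQI and HADS with a mixed model for repeated measures at weeks 5, 9, 13 and 17. Fixed effects: group, visit, group-by-visit, baseline value and institution. Use unstructured covariance and all available post-baseline data.
2. Report the week 5 group contrasts with 95% confidence intervals.
3. Either extend the multiple imputation to these scales, or state how randomised patients with no post-baseline value are handled. The mixed model alone still leaves them out, so it does not by itself satisfy the intention-to-treat sentence.
4. For motilin, gastrin and ghrelin, use ANCOVA of the post-treatment value with baseline as covariate, on the log scale if skewed.

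The cost is wording and routine software. No new data, visits or patients are needed. Follow-up is scheduled to finish by December 2027, so the change can be settled before unblinding.
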